### Trial objectives {7} {12}

This research protocol is designed to assess the safety and efficacy of a revised IPTp schedule that incorporates a screen-and-treat strategy using RDT and DP at the first antenatal care visit (IPTp-SP+). The research objectives and corresponding endpoints are listed in Table 1.

**Table 1 Tab1:** Outcomes

Objectives	Outcomes/endpoints
Primary objectives	
To compare the effectiveness of IPTp-SP versus IPTp-SP+ for treating and preventing maternal *P. falciparum* infection To compare the safety and tolerability of IPTp-SP versus IPTp-SP+	• Relative hazard of *P. falciparum* infection diagnosed by PCR at day 42 after randomization (primary outcome) • Relative hazard of *P. falciparum* infection diagnosed by PCR or microscopy at days 14, 28, 35, 42, 63, delivery, and 1-month post-partum in infants • Proportion who experience at least one episode of *P. falciparum* infection by day 14, 28, 35, 42, or 63 • Proportion with treatment or prevention failure at day 42 stratified according to study drug (SP or DP) • Median time to first episode of MIP • Acute, chronic, and prior placental infection at delivery • Medication-related adverse events and serious adverse events until 1-year post-partum (primary outcome)
Secondary objectives	
To compare the effectiveness of IPTp-SP versus IPTp-SP+ for reducing complications of MIP	• Mean birth weight and prevalence of low birth weight (within 72 hours post-partum), neonatal mortality (within 28 days post-partum), congenital malaria diagnosed by PCR, placental malaria diagnosed by histopathology using placental biopsies, maternal anemia (hemoglobin changes at days 14, 28, 42 and 63), congenital anemia, Incidences of pregnancy losses, congenital *P. falciparum* infection
To compare selection for drug resistant parasites between infected individuals in the IPTp-SP and IPTp-SP+ treatment groups	• Relative allele frequencies of genotypic markers of drug resistance in malaria parasites
To measure piperaquine exposure and duration	• Terminal elimination half-life of piperaquine determined by noncompartmental analysis of drug concentrations at 0, 14, 28, 35 and 42 days

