### Intervention {11a} {11b} {11c}

The intervention will consist of IPTp-SP with or without screen-and-treat using DP at the first ANC visit. Participants randomized to the IPTp-SP+ group who test positive by rapid diagnostic test (RDT) will be given a full treatment course of DP (D-ARTEPP® 40 mg/320 mg three tablets daily for 3 days; Guilin Pharmaceutical) under direct observation (DOT) by a study nurse (day 0) or community health worker (days 1–2). All other participants will be treated with SP at the first visit, including those in the IPTp-SP+ arm with a negative RDT result, and all participants in both groups will be given SP at all subsequent visits (day 35, day 63, then monthly until delivery) under DOT. IPTp-SP will be administered according to national guidelines (G-SCOPE® 1,500 mg sulfadoxine/75 mg pyrimethamine for one dose no fewer than 4 weeks between doses; Guilin Pharmaceutical). Participants will be observed for 1 h post-dose to monitor for vomiting or other adverse reactions. If vomiting occurs within 30 min, the full dose will be readministered. If vomiting occurs after 30 min, half of the total dose will be readministered. In the case of persistent vomiting, the participant will be withdrawn from the study and referred for alternative treatment.

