### Clinical procedures {11d} {13} {15} {26a}

Study procedures are outlined in Table 3 and the flow of events is shown in Fig. 1. The informed consent will be administered by a study nurse in the local language (Bemba) and/or in English as preferred by the participant. Assent will be obtained from participants <18 years old, and informed consent will be obtained from those ≥18 or the legally authorized representative for minors. If the participant cannot provide a written signature, then a thumbprint will be obtained. After collection of demographic data, provision of informed consent, baseline medical and obstetric history, and physical examination by a study physician including eligibility assessment, participants will be randomized to either the IPTp-SP or IPTp-SP+ treatment groups. All participants will undergo hemoglobin measurement as part of the screening process. On enrollment, fingerstick blood will be drawn for preparation of dried blood spots (DBS) for subsequent molecular testing. In addition, participants randomized to the experimental group (IPTp-SP+) will undergo RDT.

**Table 3 Tab3:** Schedule of events

	Antenatal period *Study day*									Postpartum period *Study month*			
Event	0	1–2	14	28	35	42	63^a^	Unsch.	Birth	1	6	9	12
Informed consent/oral assent	•												
Medical history	•												
Physical examination, including height, weight, temperature	•		•	•	•	•	•	•	•				
Fetal viability	•		•	•	•	•	•	•	•				
Focused history and examination			•	•	•	•	•	•	•	•	•	•	•
Adverse event evaluation	•	•	•	•	•	•	•	•					
IPTp-SP^b^	•				•		•						
RDT^c^	•												
Treatment with DP^d^	•	•											
DBS for PCR, genotyping	•		•	•	•	•	•	•	•				
Malaria microscopy^e^			•	•	•	•	•	•	•				
Hemoglobin measurement	•		•	•		•	•		•	•			
Blood sample for PK^d^	•		•	•	•	•							
Delivery									•				
Placental biopsy, cord blood									•				
Infant assessment including history and exam, weight, heel stick									•	•	•	•	•

^a^Monthly visits continue until delivery

^b^Includes participants randomized to standard IPTp-SP, participants randomized to IPTp-SP+ who test negative at the first visit, and all participants in both groups at days 35, 63 and then monthly until delivery

^c^Limited to participants randomized to IPTp-SP+

^d^Limited to participants randomized to IPTp-SP+ who test positive by RDT at the first visit

^e^Only participants with signs or symptoms of malaria will undergo microscopy

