### Statistical analysis {20a} {20b} {20c}

Longitudinal data will be displayed using the nonparametric Kaplan-Meier estimations of the survival function. The primary analysis will be comparison of the 42-day incidence of MIP using multivariate models to estimate the relative hazard between the IPTp-SP and IPTp-SP+ groups according to intention-to-treat (ITT). Testing for proportionality of hazards will be done using formal statistical testing with Schoenfeld residuals as well as visual inspection of the nonparametric survival estimates. For non-proportional hazards, an extended Cox model will be applied. To handle interval censoring due to participants who miss one or more follow-up visits, we will use parametric models for interval-censored survival-time data. The relative hazard will be estimated in parametric models accounting for recurrent events by using a robust variance estimator. For the primary safety analysis, we will compare the proportions of serious and non-serious AEs using logistic regression models and relative hazards of AEs using Cox regression methods as above. Secondary analyses of continuous outcomes (hemoglobin concentration, birthweight) will be examined in linear regression models and in logistic regression models for binary outcomes (prevalence of low birth weight, neonatal mortality, placental malaria, congenital malaria, maternal anemia, congenital anemia, drug resistance allele frequency). Prespecified subgroup analyses will be done according to the following strata: primigravidae, multigravidae, gestational age at enrollment, delivery before or after the day 63 visit, treatment dose on a mg/kg basis, positive *P. falciparum* PCR on enrollment, and presence or absence of quintuple and sextuple mutations. In a secondary analysis, we will compare the proportions of treatment failures and prevention failures according to the antimalarial drug given at the first encounter (SP or DP) in an on-treatment analysis using logistic regression. Treatment failures will be defined as recurrent infections that are determined by genotyping to be recrudescent parasites from the initial infection in participants who tested positive by PCR at the initial visit. Prevention failures will be defined as PCR-confirmed parasitemia in participants who initially tested negative by PCR at the first visit, or who tested positive by PCR at the first visit but who experienced reinfection with a new parasite as determined by genotyping. No interim analysis is planned. Every effort will be made to collect complete data for all participants and minimize missing data. Missing data will be handled using multiple imputation.

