## Discussion

### Rationale for this study

Prevention of malaria during pregnancy is important to maternal and child health in endemic areas, but the spread of drug resistant *P. falciparum* has compromised the effectiveness of the current standard approach of IPTp-SP [28–32]. Clinical trials of alternative strategies are therefore needed. This trial protocol describes a hybrid IPTp-SP approach that combines standard IPTp-SP with screening and treatment using DP at the first ANC visit.

There are four justifications to this approach. First, higher density infections that occur early in gestation around the time of the first ANC visit are believed to pose a greater risk to pregnancy than infections that occur later in pregnancy or are lower in density [33–35]. These earlier, higher density infections are often detectable by RDT and are more effectively cleared by curative artemisinin-based combination therapies (ACTs) than by SP, particularly in areas with high quintuple and sextuple mutants. Second, compared to other ACTs, DP provides a period of post-treatment prophylaxis similar to SP owing to piperaquine’s long half-life [36–38]. ACTs with shorter elimination half-lives than DP may be insufficient to bridge the period between ANC visits. Third, screening and treatment during the first visit only—rather than all ANC visits—has the ability of detecting over 50% of all *P. falciparum* infections diagnosed during pregnancy and it is believed to minimize programmatic complexity and resource consumption without sacrificing utility [34]. Mathematical models that compared screening and treatment at the first visit only to screening and treatment at every visit predicted only a marginal difference between the two approaches [33]. Fourth, drug resistance in *P. falciparum* to antifolates is a graduated, rather than all-or-none, phenomenon. Even in areas of prevalent SP resistance genetic markers, IPTp-SP retains a clinically significant level of effectiveness [11]. Some of its effectiveness may be independent of its antimalarial properties. Thus, abandoning SP altogether may not be advisable because it would relinquish a still useful drug while exposing other antimalarials to a greater potential of emerging resistance.

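### The secondary comparison of treatment and prevention failures by drug received (SP or DP) is confounded by RDT result, and will usually understate a true DP benefit

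*Protocol article*

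**What the plan says.** The Statistical analysis section describes, as a secondary analysis, a comparison of how often each of the two failure types (treatment and prevention) occurs, made "according to the antimalarial drug given at the first encounter (SP or DP) in an on-treatment analysis using logistic regression". It names no restriction to, or adjustment for, RDT result or parasite density. Table 1 carries the matching endpoint under the primary objectives, without marking it as a primary outcome: "Proportion with treatment or prevention failure at day 42 stratified according to study drug (SP or DP").

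The Intervention section fixes who receives which drug. In the IPTp-SP+ arm, women "who test positive by rapid diagnostic test (RDT) will be given a full treatment course of DP". For everyone else: "All other participants will be treated with SP at the first visit, including those in the IPTp-SP+ arm with a negative RDT result". Under Clinical procedures, only "participants randomized to the experimental group (IPTp-SP+) will undergo RDT", and footnote c of Table 3 confirms the limit.

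Treatment failure is defined as genotyped recrudescence in women PCR-positive at the first visit. Prevention failure is parasitaemia in women PCR-negative at the first visit, or reinfection in women who were PCR-positive.

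The Rationale section says that "higher density infections that occur early in gestation around the time of the first ANC visit are believed to pose a greater risk" to the pregnancy, and then: "These earlier, higher density infections are often detectable by RDT".

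**The concern.** Drug received is decided by a test result within one arm, not by randomisation. Every DP recipient is RDT-positive. The SP group is a mixture: controls of both kinds, plus IPTp-SP+ women selected for being RDT-negative, who have no counterpart among DP recipients. If RDT result predicts failure, a logistic regression on drug received mixes the drug effect with that prognostic difference.

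This comparison is labelled by drug and appears in Table 1 under the primary objectives, so readers are likely to take it as the trial's statement on DP versus SP. At stake is a DP effect reported as smaller than it is and, in some settings, as absent or reversed.

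**Working it through.** The protocol gives no figure for this analysis, so there is none to reproduce. Its sample size concerns the comparison of randomised arms: 24% against 12% (24% being the midpoint of the stated 22–26% PCR prevalence), two-sided 0.05 and 80% power, gives 160 per arm against the stated 162. That calculation does not bear on the comparison by drug.

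**Can the imbalance be adjusted away?** Controls have no RDT. Table 3 schedules no day-0 microscopy, and the Molecular assays section describes PCR for detection, not density. Day-0 PCR status is available for everyone, but all women in the treatment-failure analysis are PCR-positive, so it cannot separate RDT-positive from RDT-negative infections there.

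**Treatment failure.** All risks here are assumptions, since the protocol states none. Let s be the share of PCR-positive women who are RDT-positive. Failure under SP is 35% in RDT-positive and 10% in RDT-negative infections. Failure under DP is 25% (true OR in RDT-positive women (0.25/0.75)/(0.35/0.65) = 0.62) or 17.5%, a halving (true OR (0.175/0.825)/(0.35/0.65) = 0.39).

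Per infected woman in each arm, SP recipients comprise s RDT-positive controls, (1−s) RDT-negative controls and (1−s) RDT-negative IPTp-SP+ women:

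SP failure = [0.35s + 0.10 × 2(1−s)] / [s + 2(1−s)]

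At s = 0.7 this is (0.245 + 0.060)/1.3 = 23.5%, and the by-drug OR with DP at 25% is 0.3333/0.3065 = 1.09. By randomised arm at s = 0.7, failure is 0.7 × 0.25 + 0.3 × 0.10 = 20.5% against 0.7 × 0.35 + 0.3 × 0.10 = 27.5%, an OR of 0.2579/0.3793 = 0.68.

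| s | SP failure | By-drug OR, DP 25% (true 0.62) | By-drug OR, DP 17.5% (true 0.39) | By-arm OR, DP 25% |
|---|---|---|---|---|
| 0.9 | 30.5% | 0.76 | 0.48 | 0.64 |
| 0.7 | 23.5% | 1.09 | 0.69 | 0.68 |
| 0.5 | 18.3% | 1.48 | 0.94 | 0.73 |

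The by-drug OR passes 1 once DP failure exceeds the pooled SP failure in the second column.

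A more general form uses k, the ratio of failure risk under SP in RDT-positive to RDT-negative infections, and t, the true DP/SP risk ratio in RDT-positive women:

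Crude RR = k·t·(2−s) / [2(1−s) + s·k]

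- k = 1: crude RR = t, so no bias.
- t = 0.50, s = 0.6: 0.70 (k = 2), 0.81 (k = 3), 0.875 (k = 4).
- t = 0.50, s = 0.4: 0.80 (k = 2), 1.00 (k = 3), 1.14 (k = 4).

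**Prevention failure with no drug effect.** Assume a 10% risk in women uninfected at entry and 10%·m in women infected at entry, s = 0.7, and every RDT-positive woman PCR-positive. With PCR prevalence p, the infected share of the SP group is 1.3p/(2 − 0.7p): 0.286/1.846 = 15.5% at p = 22%, and 0.338/1.818 = 18.6% at p = 26%. DP recipients are all infected at entry.

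- m = 1: 10% in both groups, OR 1.00.
- m = 1.5: DP 15%; SP 10% + 5% × 0.155 = 10.8% to 10% + 5% × 0.186 = 10.9%; OR 1.46 to 1.44.
- m = 2: DP 20%; SP 10% + 10% × 0.155 = 11.5% to 10% + 10% × 0.186 = 11.9%; OR 1.91 to 1.86.

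**The case against.** The comparison is called secondary, Table 1 does not mark it as a primary outcome, and the primary analysis follows randomised arm. All of that stands and limits the severity.

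Treatment failure is already confined to PCR-positive women, so uninfected women do not enter it. This stands too: for that endpoint the remaining confounding is between RDT-positive and RDT-negative infections only.

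A reader might infer that the analysis will hide or reverse a DP benefit. The documents do not support this. They give no failure risks, no RDT sensitivity and no risk gradient, and the Rationale expects ACTs to clear these infections better than SP does. With a halving of failure the by-drug OR stays below 1 at all three sensitivities in the table. The Rationale also says only that denser infections are often RDT-detectable, not that every RDT-positive infection is dense.

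The protocol prespecifies a subgroup of women PCR-positive at enrolment, which the Limitations section describes as a comparison of the arms. That is the right population and a randomised comparison, but it is offered against dilution of the effect on malaria incidence. It does not repair the comparison of failures by drug.

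Covariates for a secondary model are commonly left to an analysis plan, which is not shown, and stored day-0 blood spots could perhaps be tested for antigen or density. It would therefore be too strong to say that adjustment is impossible. But the protocol plans no such testing, and without it no analysis plan can supply RDT status in controls. Stratifying prevention failure by day-0 PCR would remove the infected-versus-uninfected difference, but would leave the sorting by RDT among infected women.

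**Conclusion.** The point holds as confounding built into a secondary analysis. It follows from the allocation rule and needs no outside figure. Its direction against DP rests on two conditions that the protocol makes plausible or leaves open but does not quantify: that RDT-positive infections fail more often under SP, and that women infected at entry are reinfected more often. Where either condition is absent, the corresponding bias vanishes.

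For treatment failure the usual consequence is attenuation. Masking or reversal needs a modest DP effect, or low RDT sensitivity together with a steep gradient. For prevention failure the size depends wholly on the assumed reinfection ratio. The sizes shown are illustrations, not estimates for this trial.

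A correction is worth making before the final analysis plan is approved, but this is not a flaw in the trial's main result.

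**What to change.** In the Statistical analysis section, replace the test by drug received with two comparisons by randomised arm: treatment failure among women PCR-positive on day 0, and prevention failure within strata of day-0 PCR status. Report failures by drug received as descriptive and explicitly non-randomised, and reword the Table 1 row to match.

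The cost is wording only. Day-0 blood spots for PCR are scheduled for every participant. The article reports data collection as ongoing, and statisticians stay masked until the DSMB has approved the final analysis plan and the database is locked, so the change can be made without knowledge of results.

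The downside is some dilution: among PCR-positive women the IPTp-SP+ arm includes RDT-negative carriers who receive SP. In the illustration with DP failure at 25%, the by-arm OR is 0.64 to 0.73 against a true 0.62, which keeps the direction of the effect.

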#### Molecular assays

DBS collected onto filter paper cards (Whatman® 903 Protein Saver, Sigma-Aldrich) will be allowed to rack-dry overnight and stored individually in opaque sealable plastic bags with desiccant before subsequent use in PCR assays. PCR detection of parasites will be done using cytochrome b. Recurrent episodes will be genotyped to distinguish recrudescence infections from new infections according to standard WHO protocols will be conducted with nested PCR of *merozoite surface protein-1* and -*2* (*msp1*, *msp2*) and glutamate-rich protein (*glurp*) genes for length polymorphisms [22]. Infections will be classified as recrudescent infection if, for each marker, there is at least one identical allele between the initial and recurrent infection. Infections will be classified as reinfections if, for at least one marker, there is a different length polymorphism between the initial and recurrent infection. Infections will be classified as indeterminate in the case of low coverage or missingness due to amplification failure that precludes comparisons at all three genes. Drug resistance markers for artemisinins, SP, piperaquine, and related markers for chloroquine and amodiaquine cross-resistance will be evaluated by molecular inversion probe and amplicon deep sequencing based approaches [23, 24].

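### A PCR-confirmed recurrence with an indeterminate genotype fits neither failure definition, so the combined treatment-or-prevention-failure outcome is understated

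*Protocol article*

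**What the plan says.** In the Protocol article, Table 1 lists under the primary objectives, without marking it as a primary outcome, "Proportion with treatment or prevention failure at day 42 stratified according to study drug (SP or DP". The Statistical analysis section calls the comparison by first drug a secondary analysis, done "in an on-treatment analysis using logistic regression". It defines the two kinds of failure as follows.

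- Treatment failure, in women PCR-positive at the first visit: "recurrent infections that are determined by genotyping to be recrudescent parasites from the initial infection".
- Prevention failure, first limb: "PCR-confirmed parasitemia in participants who initially tested negative by PCR at the first visit". No genotype is needed.
- Prevention failure, second limb: women "who tested positive by PCR at the first visit but who experienced reinfection with a new parasite as determined by genotyping".

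The Molecular assays section gives recurrences three classes: recrudescent, reinfection, and a third described thus: "Infections will be classified as indeterminate in the case of low coverage or missingness due to amplification failure that precludes comparisons at all three genes".

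On missing values in general, the Statistical analysis section says: "Missing data will be handled using multiple imputation". It does not say whether an indeterminate genotype is a missing value.

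Under Intervention, DP at the first visit goes only to RDT-positive women in the IPTp-SP+ arm. All controls and the RDT-negative IPTp-SP+ women receive SP.

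**The concern.** The laboratory section has three classes and the failure definitions use two. Take a woman who is PCR-positive at baseline and again on day 28, with a pair that cannot be classified. She is not a treatment failure, because recrudescence was not shown, and not a prevention failure, because reinfection was not shown. Yet her parasitaemia is proven and must be one or the other. For the combined outcome nothing about her is unknown; for the components only the type is.

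The gap bears unequally on the drugs. Nearly every DP recipient with a recurrence was PCR-positive at baseline and needs a genotype to count. Most SP recipients were PCR-negative at baseline and count on PCR alone. A rule that drops unresolved genotypes can therefore move the DP-versus-SP comparison as well as lower both proportions.

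**Working it through.** **Scale.** The protocol gives no figure for the failure analysis, so there is none to reproduce there. The evaluable size of 162 per arm serves only to turn proportions into counts. It is reproduced closely by 24% versus 12%, two-sided 5%, 80% power: [1.96·√(2·0.18·0.82) + 0.8416·√(0.24·0.76 + 0.12·0.88)]² / 0.12² = 160 per arm.

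**Inputs from the protocol.** Baseline PCR prevalence 24% (midpoint of 22–26%, Sample size section). Recurrence in baseline-positive women 24% (midpoint of the 22% and 26% SP failures in the Background). The second is an SP figure; applying it to DP is an assumption, varied below.

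**Assumptions.** RDT sensitivity against PCR 60%; 3% of PCR-negative women RDT-positive; day-42 parasitaemia in baseline-negative women 12%; share of recurrences in baseline-positive women that are indeterminate, u = 20%, equal in both drug groups.

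**Who is in each group (162 per arm).**
- DP: PCR-positive 162·0.24·0.60 = 23.3; PCR-negative 162·0.76·0.03 = 3.7; total 27.0, of whom 86% PCR-positive.
- SP: PCR-positive 162·0.24·(1 + 0.40) = 54.4; PCR-negative 162·0.76·(1 + 0.97) = 242.6; total 297.0, of whom 18% PCR-positive.

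**Failures, all PCR-confirmed parasitaemia counted.**
- DP: 23.3·0.24 + 3.7·0.12 = 5.6 + 0.4 = 6.0 (22.4%). Share needing a genotype: 93%.
- SP: 54.4·0.24 + 242.6·0.12 = 13.1 + 29.1 = 42.2 (14.2%). Share needing a genotype: 31%.
- Risk ratio 0.2236/0.1420 = 1.575.

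**Failures lost at u = 20%.** DP 0.20·5.6 = 1.1 women (18.5% of its failures); SP 0.20·13.1 = 2.6 women (6.2%).

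| Handling of indeterminates | DP | SP | Risk ratio | Relative to 1.575 |
|---|---|---|---|---|
| Counted as failure | 22.4% | 14.2% | 1.575 | – |
| Coded no failure | 18.2% | 13.3% | 1.368 | 0.868 |
| Excluded | 19.0% | 13.4% | 1.414 | 0.898 |

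**Sensitivity.**
- Coded no failure with u = 10% or 30% in both groups: relative ratio 0.936 or 0.796.
- Recurrence on DP halved to 12%, u = 20%: 0.882.
- Prevalence 22–26% and RDT sensitivity 40–80%, u = 20%: 0.856–0.883.
- Unequal rates, 20% in DP against 40%, 60% or 80% in SP, coded no failure: 0.930, 1.001, 1.083. The lean toward DP vanishes near 60% and then reverses.

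**A second set of assumptions.** With prevalence 24%, RDT sensitivity 70%, no false positives, recurrence 26% on SP and 13% on DP, 10% in baseline-negative women and u = 20%, the odds ratio is 1.02 with indeterminates counted, 0.86 coded no failure and 0.88 excluded.

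**Treatment failure alone.** Every event in both groups needs a genotype, so equal u removes the same share from each. Both proportions fall, but no difference between the drugs is created.

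**What indeterminate covers.** The closing clause of the laboratory rule can mean that a failure at any one gene suffices, or that all three must fail. If each marker pair fails independently with probability p = 10% (assumption), the first reading gives 1 − 0.9³ = 27% indeterminate and the second 0.1³ = 0.1%. The size of the problem depends heavily on which is meant.

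**The case against.** Several points on the other side stand. The protocol does not say that indeterminate recurrences are scored as non-failures; exclusion or imputation is equally open. The laboratory rule itself speaks of missingness, and multiple imputation is planned for missing data. A final analysis plan, not shown, is to be approved before the statisticians are unmasked and could settle the coding.

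A reader might infer that the rule removes more failures from DP than from SP. As a count that is false: about 1.1 against 2.6 women. It holds only as a share, for the combined or prevention outcome, and only if indeterminate rates are similar. A reader might also infer an established bias in favour of DP. The documents do not support that: they give no indeterminate rate, and the Discussion describes RDT-detectable infections as higher in density, so the infections that RDT missed, all treated with SP, may amplify less well.

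The consequence is also limited. The comparison is secondary and not randomised. With about 6 of 27 against 42 of 297 failures, the 95% interval for the odds ratio spans roughly a factor of 2.6 either way. Table 1 already lists a genotype-free proportion with any infection, though not by drug.

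What does not stand is that this is only an unstated detail. The protocol states both definitions and the third class, and they do not fit together. Exclusion does not cure it, since it drops only women who failed. The general imputation sentence does not settle it either: the combined outcome is already observed for these women, and only the type needs imputing.

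**Conclusion.** The concern holds in a limited form. Read literally, the definitions leave a PCR-confirmed recurrence with an indeterminate genotype in neither failure category, and the combined day-42 outcome is understated under both coding as no failure and exclusion. This follows from the text without numerical assumptions, wherever any recurrence is indeterminate.

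The effect on the drug comparison is conditional. At an assumed 20% indeterminate in both groups, the DP:SP risk ratio is about 10% (excluded) to 13% (coded no failure) too low. At 10% to 30% the coded version is about 6% to 20% too low. If SP-treated infections amplify much less well, the lean disappears or reverses. The primary day-42 PCR endpoint is not defined by genotype, so the primary result is not in question.

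**What to change.** In the Statistical analysis section, count every PCR-confirmed recurrence by day 42 in the combined treatment-or-prevention-failure outcome, whatever its genotype class. For the two components, treat the type of an indeterminate recurrence as missing: impute recrudescence versus reinfection only, never failure versus no failure. Report bounds with all indeterminates counted as recrudescent and then all as reinfection.

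In the Molecular assays section, say whether a pair is indeterminate when any gene fails or only when all three fail, and how a pair with one or two amplified markers is called.

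The cost is a few lines of wording and one sensitivity table, with no new samples or assays. Failure proportions will rise slightly. The Trial status section reports data collection still ongoing, so on that status the rule could be set before database lock and unmasking.
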